### Feasibility

In order to evaluate feasibility from the participants’ perspective, we will conduct semi-guided qualitative interviews with patients from the intervention group as well as with the CTN. The acceptability of both study and intervention procedures will be evaluated by assessing whether the intervention and study procedures have been agreeable as well as logistically and technically practical [39]. A semi-guided interview with the CTN will give a more detailed insight into provider’s perspective regarding feasibility and appropriateness of the CTI.

### Outcomes

As this is a feasibility trail, there will be no hypotheses or statistical testing. Therefore, effects of the intervention are not to be expected in this small sample. Instead, we expect that a) our trial design (incl. study procedures such as recruitment strategy, data collection procedures, randomisation and logistic aspects) is suitable and b) that the intervention is feasible in this population of inpatients and at this specific time point during treatment, the transition from inpatient to outpatient care.

The feasibility of a subsequent large-scale RCT for patients at the transition from inpatient to outpatient care will be determined by assessing the following outcomes and aspects [34]:

■ recruitment strategy’s sufficiency and efficiency for both groups■ adherence for intervention group■ feasibility of study procedures (e.g., patient and provider acceptance of randomisation and outcome measurements)■ intervention procedure feasibility (CTN documentation, patient acceptance of CTI, patient safety)

To estimate the sufficiency and efficiency of the recruitment strategies, we will calculate the recruitment yield, i.e., number randomized per number screened, and the consent rate, i.e., number randomized per number eligible. We will record retention rates and reasons for non-participation or dropping out. Adherence will be determined by the ratio of scheduled and actually conducted CTI session. Concerning documentation, after every CTI session, the CTN will systematically document which elements of the intervention were used in the respective session. Patients experience relapses will have full and free access to all levels of mental healthcare which covered under the statutory health insurance in Germany. We will approach all patients systematically for post assessments regardless of whether they have received a relapse to minimize missing data for the follow-up. To evaluate process outcomes on the overall practicability of the intervention and the related study procedures, we will draw on qualitative data generated by in-depth interviewing of patients and the CTN.

### Data analysis

In order to assure data quality, we will 1) use a password protected online survey tool (Enterprise Feedback Suite (EFS) Survey, Questback GmbH) during the data collections and enter data from the paper questionnaire there, 2) enforce data integrity using forced or multiple-choice items wherever possible, and 3) ensure that only two members of the study team will have access to the data as well as the participants identifying information and will prepare it prior to data analysis. Quantitative data on clinical outcomes along with information on health service use will be analysed using descriptive statistics (absolute and relative frequencies, measures of central tendency, and measures of variability). We will not test any hypotheses or perform any statistical tests, but rather will assess the feasibility of a following large-scale RCT. We will report various dimensions regarding feasibility, e.g., overall recruitment yield (number randomised per number screened), the recruitment rate (number recruited and randomised per general practice per month), consent rate (number randomised per number eligible), and loss to follow-up. To illustrate participant flow, we will report results in a CONSORT diagram [40]. We will describe patients’ reasons for non-participation as well as conduct a non-responder analysis. Qualitative data stemming from the process evaluation (i.e., interviews with patients and CTN) will be analysed utilizing the thematic analysis approach deriving key themes bottom-up. For the descriptive quantitative analysis, we will use R (version 4.3.1 or higher).

To gain a vaster understanding of the context in which the outcomes of the RCT developed, we will conduct a process evaluation consistent of qualitative semi-guided interviews with the patients and CTNs [41]. We will purposefully sample participants concerning hard-to-reach groups (oversampling men and patients with chronic and multimorbid conditions) The interviews will focus on barriers as well as facilitators of the model. Process data will be collected after the intervention, to gain insight into the various intervention stages [42]. The top-down themes of for the thematic analysis of the interview data will be 1) quality of implementation, (2) causal mechanisms/pathways, and (3) contextual influences on the implementation of the intervention. Coders executing the qualitative analysis will not be part of the delivery of the intervention nor analyze the qualitative data prior to knowing the trial outcomes.

For the thematic analysis of the qualitative data we will use MAXQDA 2020 or higher. All study publications will align with recommendations of the respective statements for randomised trials (CONSORT [40]) and qualitative research [43].

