After discharge, further CTI sessions will take place between the patient and the CTN, during which barriers on the patient’s side will be continuously identified and addressed. Additionally, if necessary the CTN will reflect on the ambivalence towards follow-up treatment with the patient, to build motivation. In the first month after discharge, there will be two CTI sessions; in the months two and three after discharge, there will be one CTI session per month. If a patient successfully takes up outpatient follow-up treatment before the fifth CTI session, at least one further CTI session will be offered for joint final reflection and assessment of the sustainability of follow-up treatment. If the patient needs more structuring of the intervention, a patient-centred written brief discharge plan will be jointly developed by the patient and the CTN. This will help to (1) clarify the need and (2) the desired design of a follow-up treatment, (3) identify possible barriers, (4) identify patient’s areas/problems in particular need of support by the CTN, and (5) schedule the session dates between patient and CTN (1^st^ month two sessions, 2^nd^ and 3^rd^ month one session each). To support and motivate the patient, the CTN can screen for psychosocial services and treatment possibilities in the vicinity of the patient’s home. Furthermore, the patient will be motivated to contact the general practitioner after discharge and to inform him/her about the further course of treatment. Further components for support and motivation can vary individually depending on the symptom severity and the resources of the patient, but will include components of the following spectrum: systematic reminders about doctor’s appointments and medication intake, screening for suicidal ideation, evaluation of already known and/or newly emerging barriers, psychoeducation regarding the handling of mental disorders and coping strategies and behavioural activation (maintaining a positive attitude, solution orientation, stimulation of self-help). These optional components have been shown to be effective in several comparable studies [14, 17]. The CTI sessions will be conducted via a secure (i.e., encrypted), web-based videoconferencing platform on a subscription basis (arztkonsultation ak GmbH) and will last between 30 and 60 minutes. Subscription fees are covered by the trial funding. No fee will apply for patients. In routine care in Germany, the use of teleconferencing systems is covered by the statutory health insurance. During the intervention period, the CTN will attend a case supervision session led by a senior physician every two weeks, where all patients will be discussed. In particular, it will be discussed how to deal with hard-to-reach and less adherent patients to successfully implement the transition to outpatient psychosocial follow-up treatment in this group as well.

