### Patient and public involvement

This protocol was drafted without patient involvement and patients were not invited to contribute to the writing or editing of this document for readability or accuracy. However, as part of the feasibility and acceptance assessment we will conduct semi-structured interviews with all patients in the intervention condition. Interviews will focus on five main questions (What was your experience with the care transition intervention like? What worked out for you? What did not go well? Would you engage in the intervention again and/or recommend it to others? Why? Why not? Do you have any suggestions for improving the intervention? Which logistical problems did you experience? If applicable, how were they dealt with?). At the end of the interview, we will invite all patients to be systematically included in the refinement of the intervention. This could include development of the procedures and materials of a consecutive sufficiently powered effectiveness trial. We will align patient and public involvement with current guidelines [44].

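### The interview sample is described in two incompatible ways, and neither secures the views of patients who stop or rarely attend the CTI

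*Protocol article*

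**What the plan says.** The protocol article mentions the patient interviews in three places.

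- **Feasibility:** "we will conduct semi-guided qualitative interviews with patients from the intervention group as well as with the CTN". It does not say whether this means all intervention patients or some of them.
- **Data analysis** (process evaluation): "We will purposefully sample participants concerning hard-to-reach groups (oversampling men and patients with chronic and multimorbid conditions". On timing it adds: "Process data will be collected after the intervention, to gain insight into the various intervention stages".
- **Patient and public involvement:** as part of the feasibility and acceptance assessment, "we will conduct semi-structured interviews with all patients in the intervention condition". The interview questions are listed here, including what went badly and whether the patient would take part again.

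Three other statements bear on patients who stop.

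- **Intervention:** in the fortnightly supervision of the navigator, "it will be discussed how to deal with hard-to-reach and less adherent patients".
- **Outcomes**, on stopping: "We will record retention rates and reasons for non-participation or dropping out", and "Adherence will be determined by the ratio of scheduled and actually conducted CTI session".
- **Outcomes**, on follow-up: "We will approach all patients systematically for post assessments regardless of whether they have received a relapse". This concerns the post assessments and does not mention the interviews.

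Patient acceptance of the CTI is among the feasibility outcomes listed in Outcomes.

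**The concern.** Patients who give up an intervention are often those who found it least acceptable, and their reasons are what the sponsor most needs in order to refine it. The article expects some patients to be hard to reach or less adherent. Its sampling rule also refers to hard-to-reach groups, but defines them by sex and morbidity. Attendance at CTI sessions is not a criterion.

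The timing adds to this. One session takes place before discharge, two in the first month after it, and one in each of months two and three. A patient who stops after the first session could wait up to about three months for an interview held after the intervention period.

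At stake is the acceptability evidence that will support the decision on a large trial and the revision of the CTI. If mostly completers are heard, that evidence could be too favourable.

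**Working it through.** The article contains no figure to reproduce: it gives no stopping rate, interview subsample size or interview response rate. The main check compares the passages. The arithmetic only shows what each reading could mean.

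**Step 1. Compatibility.** Oversampling means selecting some groups at a higher rate than others. If all intervention patients are interviewed, every group is selected at a rate of 1 and none can be oversampled. For a single set of interviews, the Data analysis and Patient and public involvement sections cannot both hold. The Feasibility section does not settle it.

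**Step 2. If the purposive rule governs.** N = 50 with 1:1 allocation gives 50/2 = 25 intervention patients. Suppose s of them stop and k are interviewed, chosen without regard to stopping. The chance that no stopper is interviewed is C(25−s, k)/C(25, k). For s = 3 and k = 8 this is (17 × 16 × 15)/(25 × 24 × 23) = 4080/13800 = 0.296.

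| Stoppers s (assumed) | k = 8 | k = 10 | k = 12 | k = 15 |
|---|---|---|---|---|
| 3 | 0.296 | 0.198 | 0.124 | 0.052 |
| 5 | 0.116 | 0.057 | 0.024 | 0.005 |
| 8 | 0.022 | 0.006 | 0.001 | 0.000 |

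Missing every stopper is a real risk only if few stop and the subsample is small. The table treats selection as unrelated to stopping. Oversampling men or multimorbid patients could raise or lower these chances if those traits are related to stopping.

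**Step 3. If all patients are to be interviewed.** With k = 25 no stopper is missed by design, so only non-response can distort the picture. Assume that 90% of completers and 30% of stoppers find the CTI acceptable, that 95% of completers give an interview, that a share d stops, and that a share r of stoppers gives an interview.

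- True acceptability = 0.9(1−d) + 0.3d
- Observed acceptability = [0.9 × 0.95(1−d) + 0.3rd] / [0.95(1−d) + rd]

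For d = 0.2 and r = 0.3, the true value is 0.78 and the observed value is (0.684 + 0.018)/(0.76 + 0.06) = 0.856, which is 7.6 points too high.

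| Share stopping d | r = 0 | r = 0.3 | r = 0.6 | r = 0.95 |
|---|---|---|---|---|
| 0.2 (true 78%) | +12.0 | +7.6 | +3.8 | 0 |
| 0.4 (true 66%) | +24.0 | +13.6 | +6.2 | 0 |

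The excess disappears when stoppers respond as often as completers. Every input other than the arm size is assumed. The interviews are also analysed thematically, so the trial will not report such a percentage. The table shows direction only.

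**Step 4. What other data cover.** The session ratio shows that sessions were missed, but not why. Reasons for dropping out are recorded, although the wording stands beside retention and does not clearly extend to a patient who stops the CTI but stays in the trial. The questions about the patient's experience appear only in the interview guide.

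**The case against.** The strongest reply is that the acceptance interviews cover the whole arm, so stoppers are in the sample by plan. The oversampling sentence could then belong to a separate process evaluation of implementation, mechanisms and context. In addition:

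- Stopping CTI sessions is not the same as leaving the study. Research assistants telephone participants at three, six and nine months, which gives a contact route that does not depend on CTI attendance.
- Reasons for dropping out, session adherence, session documentation, a non-responder analysis and the navigator's own interview all inform on stopping without an interview of the patient.
- Interviewing after the intervention does not mean interviewing completers only.
- How discontinuers are approached is operational detail that an article may leave to the full protocol.

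Much of this stands. A reader might infer that stoppers are under-sampled by design, that acceptability will look too good, or that the reasons for stopping will be lost. The article does not support any of these: it plans interviews with all intervention patients, says nothing about who will respond, and records reasons for dropping out.

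The reply does not remove the conflict. The article nowhere says that there are two sets of interviews, and the Data analysis section treats the patient and navigator interviews as the process evaluation data. If two sets are meant, that needs saying, along with the timing of the acceptance interviews. The absence of operational detail is not the finding; two incompatible stated rules are.

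**Conclusion.** The point holds in a limited form. As written, the purposive rule and the all-patients rule conflict, on the assumption that both describe the same interviews. Under the first, patients who stop or rarely attend are included only by chance. Under the second, they are included by plan but may be approached late, so non-response may tilt the acceptability findings towards completers. The direction is plausible, the size cannot be determined from the article, and the bias is possible rather than certain. The separate records of dropout reasons and session adherence soften the consequence without replacing these patients' own accounts. This is an inexpensive improvement to a stated rule and does not undermine the trial.

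**What to change.** 1. Reconcile the Data analysis and Patient and public involvement sections: state whether all intervention patients or a purposive subsample will be interviewed, and whether there is one set of interviews or two.
2. If a subsample is used, add early stopping of the CTI (for reasons other than having taken up treatment) or low session attendance as a purposive criterion beside sex and morbidity. Define it in advance, for instance from the ratio of conducted to scheduled sessions, because with monthly sessions the moment of stopping is otherwise hard to fix.
3. Under either rule, approach these patients for interview when their CTI participation ends, or at the latest with the three-month telephone interview.
4. Report acceptability themes, and the numbers approached and interviewed, separately for completers and stoppers.

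The interview guide can stay the same. The cost is that interviews are spread over a longer period. Earlier interviews also add one contact, in the intervention arm only, before the three-month assessment; using the three-month call instead avoids a separate earlier contact but leaves a longer delay.

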### Study design

This study is an individually randomised feasibility trial. After the inclusion of patients, the individual intervention period will be three months; for the total recruitment time 6 months are planned. There will be two main measurements; a baseline assessment just prior to randomisation and a post assessment three months after inclusion. There will be two follow-up measurements at six and nine months after inclusion which focus on the medium-term effects. Patient recruitment August 2022 and will probably be completed in September 2023. Data collection will probably be completed by May 2024. The study protocol is reported and implemented according to Standard Protocol Items: Recommendations for Interventional Trials (SPIRIT) guidelines (S1 File) [23].

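### As worded, the protocol lets coders analyse the interviews only once they know the trial outcomes; probably a drafting slip, but it creates an avoidable risk to the qualitative feasibility evidence

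*Protocol article*

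**What the plan says.** The process evaluation is described at the end of the Data analysis section of the protocol article. Its aim is given as "To gain a vaster understanding of the context in which the outcomes of the RCT developed". On timing, "Process data will be collected after the intervention, to gain insight into the various intervention stages". On the coders, the sentence begins "Coders executing the qualitative analysis will not be part of the delivery of the intervention" and continues "nor analyze the qualitative data prior to knowing the trial outcomes".

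The same section describes the coding in two ways. One paragraph has it "utilizing the thematic analysis approach deriving key themes bottom-up". The next sets three top-down themes: implementation quality, causal mechanisms and contextual influences.

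The Outcomes section makes the interviews part of the feasibility evidence. For process outcomes on practicability, "we will draw on qualitative data generated by in-depth interviewing of patients and the CTN". The Feasibility section likewise relies on interviews for the participants' and the provider's view.

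**The concern.** A rule about who codes and when normally protects the coding from influence. The first half of this sentence does that by separating coders from delivery. The second half, read literally, requires the influence that one would expect it to exclude: nobody may code until they know how the trial turned out.

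Thematic coding involves judgement, whether themes emerge from the text or are set in advance. A coder who already knows that adherence was poor, or that one arm took up more follow-up treatment, can readily find the barriers or mechanisms that explain it. The interviews then tend to echo the quantitative results instead of adding separate evidence on whether a full trial is practicable and the intervention acceptable. Non-involvement in delivery does not address this, and no other section sets the order of coding and disclosure.

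**Working it through.** There is no stated figure to reproduce. The check is of wording, reach and timing.

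**1. Logic of the sentence.** The construction is *will not A, nor B before C*, with A = deliver the intervention, B = analyse the qualitative data and C = know the trial outcomes. *Nor* carries the negation to B. Not (B before C) means that B happens only once C holds. An outcome-blind rule would need the reverse order: B finished before C. No other sentence in the article restates, corrects or justifies the order.

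**2. How much material is covered.** The Sample size section gives N = 50 and the Randomisation section 1:1 allocation, so the intervention arm has about 50 × 1/2 = 25 patients. The section on patient and public involvement plans interviews with all of them, while Data analysis speaks of purposive sampling. The reach is therefore up to about 25 patient interviews plus the navigator. The rule makes no exception, so it covers all of them.

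**3. Which feasibility outcomes depend on coding.**

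| Depends on coding | Does not depend on coding |
|---|---|
| Practicability of the intervention and study procedures, as drawn from interviews | Recruitment yield, recruitment rate, consent rate |
| Acceptability from the patient and navigator interviews | Retention and loss to follow-up |
| | Ratio of scheduled to conducted sessions; session documentation |
| | Missing values as a sign of questionnaire acceptance |

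**4. Is the opposite order possible?** From the Study design section, "the individual intervention period will be three months" and "There will be two follow-up measurements at six and nine months after inclusion which focus on the medium-term effects". If a patient is interviewed directly after the intervention, the gap to that patient's last measurement is 9 − 3 = 6 months. This is a per-patient figure and shrinks if the interview is later.

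At trial level, recruitment is expected to run from August 2022 to September 2023 and data collection to end by about May 2024. A patient included in September 2023 finishes the intervention about December 2023 (September + 3 months), some 5 months before May 2024. A patient included in August 2022 finishes about November 2022, some 18 months before. If *trial outcomes* means the complete data, coding could therefore be finished before they exist. Under the literal rule the same interviews would wait roughly 5 to 18 months. If only the three-month assessment is meant, the window is shorter, but coding can still precede disclosure because the study team controls when coders see results.

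**5. What counts as a trial outcome.** The term is not defined in the sentence. The Outcomes section includes process outcomes that come from these interviews. Read broadly, coders would need to know results that only their own coding can produce, and the rule could not be met. It needs a definition on any reading.

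**The case against.** The strongest reply is that the order may be deliberate. The stated aim is to understand how the outcomes came about, and explanatory process evaluations are sometimes interpreted with results in hand. This stands in part: the protocol never says what the clause is for, so its intent can only be inferred. But the aim explains at most why qualitative and quantitative findings are brought together at the end. It does not explain a ban on coding any earlier, and the article does not present the clause as an explanatory design.

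A second reply is that other features limit outcome-driven coding: separation from delivery, three themes fixed in advance, published interview questions and a commitment to reporting recommendations for qualitative research. These help, but none concerns knowledge of the results.

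A third reply is that little is at stake in a descriptive trial without hypothesis tests. This stands as a limit on severity. No error rate, sample size or efficacy claim depends on the clause, and the count-based feasibility measures are untouched.

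A reader might also infer that the protocol knowingly reverses a safeguard, or that bias in the feasibility conclusions is assured. The documents support neither. The first asserts an intent that is not stated. The second turns a risk of unknown size into a result.

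**Conclusion.** Wrong as written, of moderate severity. Followed literally, the sentence requires all interview coding to be done with the outcomes known. A drafting slip is the likeliest explanation, because the clause is joined to an independence rule, but staff working from the published text would follow the wrong order. The consequence is an avoidable risk of outcome-driven interpretation in the interview evidence on practicability and acceptability. Its size cannot be calculated from the documents.

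The verdict rests on the literal reading of the sentence, on the absence of any correcting statement in the article, and on the interviews taking place soon enough after the intervention for coding to precede disclosure.

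**What to change.** Replace the sentence with one that says: coders will not deliver the intervention, and will complete and lock the thematic coding before they are given the between-group clinical and service-use results and the aggregate adherence and retention results; qualitative and quantitative findings are integrated after the lock.

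Define *trial outcomes* there as those aggregate results, excluding the process outcomes drawn from the same interviews. Limiting the rule to aggregate results also keeps it workable, since each interview will reveal something of that patient's own course. If analysis after the results really is intended, the protocol should say so and give the reason.

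The cost is one sentence, plus keeping the coders away from aggregate results until the lock. No extra data are needed. On the planned dates, coding can be finished before the final outcomes are available, so completion of the trial need not be delayed.
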